**Figure 2 F2:**
[figure not shown]
‘Natural experiment’ flow diagram. ED, emergency department; GP, general practitioner; NWIS, NHS Wales Informatics Service.

We will collect qualitative data at the intervention site within each participating ambulance service to explore perceptions of how the intervention works, what creates its effect (if any), why it might function differently in different settings and for different groups of people, and any challenges to implementation and delivery of the intervention. Subject to any restrictions associated with COVID-19, we will conduct four focus groups (supplemented where necessary by telephone or online interviews) with stakeholders—including frontline staff (paramedics and call handlers), partner health and social care providers, commissioners and managers (n=36). Focus group topic guides will cover case management delivery processes, barriers and facilitators to changed working, perceived impact for patients, issues around diversity and terminology, strengths and weaknesses of the approach and wider organisational impact across health economies such as information sharing, communication, and continuity of care.

To ensure we gain a strong picture of patient experience and circumstances, we will conduct largely unstructured interviews with people in intervention areas of each service who are referred for case management (n=32). Research paramedics based at each site will undertake interviews as far as possible. We will use this method to provide an opportunity for patients to provide their own narrative about their circumstances, experiences and views regarding their needs, service use and care received before and after the case management intervention, and the intervention itself, including terminology used. We will work with participating services to identify and invite callers to this key patient-focused element of the study. We will sample purposively to include a wide range of views and experiences, and select individuals with differing demographic characteristics, length of time they have required care and management approach provided for them to include typical and atypical patient stories. We will try to include patients from black, Asian and minority ethnic groups.

With respondents’ consent, we will audio-record and transcribe all individual and group interviews.

### Data analysis

#### Quantitative analysis

Ambulance services will provide NHS Digital and NWIS with information on recruited patients, to allow matching to anonymised data from multiple sources. We will create a single integrated study database for analysis within the Secure Anonymised Information Linkage (SAIL) Gateway.^17^

We will summarise patient recruitment via a Consolidated Standards of Reporting Trials flowchart,^18^ and will provide descriptive data summaries for patients, by service and by site, for demographics, call patterns and volume. Numbers of events will be dichotomised where contextually useful (for instance, to declassify or reclassify callers), and converted to rates when appropriate.

Our primary analyses will be by treatment allocated, so that patients meeting the criteria for ‘frequent caller’ status in an intervention (case management) site will be included in analysis in that arm of the study whether they were offered or received any intervention. The outcome measure time point will be 6 months from a patient’s first appearance on a monthly update to the ‘frequent callers’ list. This will apply to patients at control sites as well as intervention sites. This time point is appropriate to allow us to detect any effect, as case management is a targeted, time limited intervention designed to work within 6 months.

We will use multilevel generalised mixed linear models to obtain adjusted comparison of outcomes in patients at intervention sites versus those in patients receiving usual care at control sites. Using linked routine data will allow us to gather retrospective data on service use for callers included in each cohort, strengthening comparisons by enabling adjustment for historical and contemporaneous differences in service use, case mix and demographics. Reflecting an initial focus on comparing (any) case management approach with the service list approach, coding for sites will initially assume that outcomes under usual care are similar across ambulance services, as are outcomes at intervention sites. However, we will use background information on the service interventions, the descriptive summaries and formal testing, based on flexible and nested site coding, to test and modify this assumption, as appropriate—for instance, allowing intervention outcomes to vary systematically from service to service. The precise form of models will reflect the nature of the variable under consideration (logistic models for binary variables, negative binomial models for count variables and linear models for raw and transformed measurement outcomes, including rates); the multilevel element of the model will reflect the geographical clustering of sites within services. The adjusted comparisons will incorporate information on covariates and factors based on demographic and case-mix data. We will formalise these analyses in a Statistical Analysis Plan, using the relevant Swansea Trials Unit Standard Operating Procedure (SOP), which will detail conventions on model fitting (including inclusion and exclusion rules for covariates and factors), management of missing data and the reporting of outcomes.

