**Objectives:**

(1) Develop an understanding of predicted mechanisms of change to underpin evaluation. (2) Describe epidemiology of sustained high users of 999 services. (3) Evaluate case management approaches to the care of people who call the 999 ambulance service frequently in terms of: (i) Further emergency contacts (999, emergency department, emergency admissions to hospital) (ii) Effects on other services (iii) Adverse events (deaths, injuries, serious medical emergencies and police arrests) (iv) Costs of intervention and care (v) Patient experience of care. (4) Identify challenges and opportunities associated with using case management models, including features associated with success, and develop theories about how case management works in this population.

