## Methods and analysis

### Study design

STRategies to manage Emergency ambulance Telephone Callers with sustained High needs—an Evaluation using linked Data (STRETCHED) is a mixed-methods ‘natural experiment’ evaluation. We will use anonymised linked routine outcomes and qualitative data in four UK ambulance services with one intervention and one control site in each service.

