### Data collection

We will use a parallel cohort ‘natural experiment’ study design to determine effects on processes and outcomes of care, using anonymised linked data from NHS Digital and the NHS Wales Informatics Service (NWIS). The variation in exposure and outcomes will allow us to carry out analysis to link effects to intervention, that is, causes.^1^ We will include callers meeting the criteria for classification as ‘frequent caller’ by the ambulance service during 2018. We expect to recruit 300 high users per service (n=1200), allowing us to detect a change in rate of further emergency events/death of ±20% with 90% power and 95% confidence (see figure 2). We will finalise data items following completion of the logic model but expect to include (up to 6 months): further calls to emergency ambulance service, ED attendances, emergency admissions and deaths; declassification or reclassification as ‘frequent caller’; costs; and details of demographics, case mix and patterns of calls, for example, ‘out of hours’ (evenings/nights/weekends/holidays). Historical data about prior service use will allow us to adjust analyses for differences between cohorts, strengthening this study design.

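### With one site per arm in each service, formal tests of service-specific effects cannot separate variation in the effect of case management from ordinary differences between two areas

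*Protocol article*

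**What the plan says.** Under Study design, the article places the evaluation "in four UK ambulance services with one intervention and one control site in each service". That gives 8 sites, one in each combination of service and arm.

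Under Quantitative analysis, the starting model is the simplest one: "coding for sites will initially assume that outcomes under usual care are similar across ambulance services, as are outcomes at intervention sites". This starting assumption is then open to revision. The inputs to the revision are background information on the interventions, "the descriptive summaries and formal testing, based on flexible and nested site coding", and the purpose is "to test and modify this assumption, as appropriate—for instance, allowing intervention outcomes to vary systematically from service to service". On clustering, "the multilevel element of the model will reflect the geographical clustering of sites within services". The same section adjusts for prior and concurrent service use, case mix and demographics. It leaves model-fitting conventions, missing data and the reporting of outcomes to a statistical analysis plan.

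Objective 4 is to "Identify challenges and opportunities associated with using case management models, including features associated with success". The Synthesis section uses the qualitative data to interpret the effectiveness results. The Discussion describes the comparison as all control sites against all intervention sites, and concedes in general terms that differences between sites may confound it.

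**The concern.** Exposure is set by site, not by caller. To ask whether case management works differently from service to service, the analysis needs to know how far two areas of one service would differ with no case management in either. One site per arm per service provides no replication from which to learn this.

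If ordinary differences between areas in provision, call handling or recording are tested against variation between callers, they will often look like real variation in the effect. The model would then be modified on the strength of that test. The synthesis could go on to look for features that explain why one model succeeded and another did not, when nothing more than area differences had been seen.

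This is separate from the pooled comparison, which can take a valid error from the four within-service differences.

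**Working it through.** **The plan's own figure.** The only related figure is the sample size: 300 per service, 1200 in all, "allowing us to detect a change in rate of further emergency events/death of ±20% with 90% power and 95% confidence". No baseline rate, SD or ICC is given, so it can be neither confirmed nor refuted. For instance, 46% against 36.8% needs 601 per arm, 50% against 40% needs 519, and 40% against 32% needs 755, none with any allowance for site clustering. The point below does not depend on this figure; it uses only the 300 per service.

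**Step 1: count parameters against sites (no assumed figures).**

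| Site coding | Parameters | Site-level df left from 8 sites |
|---|---|---|
| Arm only (the starting model) | 2 | 6 |
| Service terms plus one common arm effect | 4 + 1 = 5 | 3 |
| Common usual care, intervention outcomes vary by service | 1 + 4 = 5 | 3 |
| Usual care and intervention outcomes both vary by service | 4 + 4 = 8 | 0 |

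In the last row the model reproduces the 8 site means exactly. A random site effect cannot be estimated beside those terms, so the planned multilevel element gives no protection. The standard errors can come only from callers within sites.

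In the third row, 3 df remain, all from the spread of the four control sites. Using them means assuming that intervention sites vary as control sites do and that services do not differ in level. Any service difference goes into the estimate for that service's intervention site, because its own control site is no longer its specific comparator. Each intervention estimate still rests on one site.

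**Step 2: size of the error when caller-level variation is used.** Assumptions: no effect of case management in any service; m = 150 callers per site (300 per service, split equally); no covariates; nominal two-sided 5% tests; ICC values chosen for illustration.

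The variance of a within-service difference exceeds its caller-level value by the factor f = 1 + m × ICC / (1 − ICC). The true rejection rates are then:

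- one service: P(|Z| > 1.96/√f)
- heterogeneity across four services: P(χ² on 3 df > 7.815/f)

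At ICC 0.01, f = 1 + 150 × 0.01/0.99 = 2.515. The effective cut-offs are 1.96/√2.515 = 1.236 and 7.815/2.515 = 3.107.

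| ICC | f | One service | 3-df heterogeneity |
|---|---|---|---|
| 0 | 1.000 | 5.0% | 5.0% |
| 0.002 | 1.301 | 8.6% | 11.1% |
| 0.005 | 1.754 | 13.9% | 21.6% |
| 0.01 | 2.515 | 21.7% | 37.5% |
| 0.02 | 4.061 | 33.1% | 58.8% |
| 0.05 | 8.895 | 51.1% | 83.1% |

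Simulation with 20,000 replicates agrees: at ICC 0.01, 21.7% and 37.6%; at ICC 0.05, 51.1% and 83.0%. Testing whether intervention sites differ under the common-usual-care coding, still with caller-level error, is inflated as much: 37.1% and 82.5%.

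**Step 3: contrast with the pooled effect.** A t-test on the four within-service differences (3 df, critical value 3.18) keeps its size in simulation, at 4.8% to 5.3%. The loss of validity is therefore specific to the service-level estimates and the test between them.

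**The case against.** The strongest reply is that the article does not commit to the 8-parameter model. Its one worked example frees only the intervention outcomes. Read literally, that has 5 parameters and leaves 3 df. With error taken from the control sites, no service variance and equal site variance in both arms, simulated tests hold their size: 5.0% for one intervention site, and 4.9% to 5.1% for an F(3,3) comparison. This stands. It would be wrong to say that a site variance can never be estimated under the planned relaxation. But the rescue needs services not to differ in level, which sits badly with a model meant to reflect sites clustered within services. The article also names nested coding, which leads to the row with no df if both outcomes vary.

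A reader might also infer that the study will report four service-specific effects as causal findings. The article does not say so. Revision of the model is conditional and draws on background information and descriptive summaries as well as tests. The Synthesis section aims to generate theories, and the Discussion admits confounding by site. The harm in reporting is a risk, not a stated plan.

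Two further replies carry partial weight. Adjustment for prior use and case mix may lower the residual ICC; at 0.002 the inflation is modest. It cannot remove differences that belong to the area rather than the caller. And the analysis plan, which is not shown, may settle the error term and the labelling. It cannot add a second site to any cell.

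**Conclusion.** The point holds in a limited form. The article fixes one site per arm per service and names a formal test, with nested site coding, as a ground for changing the model. That test cannot distinguish a varying effect of case management from ordinary differences between areas. This follows from the site count alone and needs no assumed figure.

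The size of the error does rest on assumptions: no effect, 150 callers per site, no covariates, and ICCs that the article does not supply. At ICC 0.002, 0.01 and 0.05, a caller-level test in one service rejects in about 9%, 22% and 51% of studies, and the heterogeneity test in about 11%, 37% and 83%. These rates apply if caller-level error is used, which is unavoidable only in the fully nested model.

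The documents do not support the stronger conclusions that every relaxed model lacks a site-level error, that the pooled comparison fails for this reason, or that misleading service-specific claims are already planned. The matter should be put right in the wording, because it bears on how the model is chosen and on what reaches the synthesis.

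**What to change.** In Quantitative analysis, and in the statistical analysis plan:

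- Keep the pooled within-service contrast as the inferential estimate, with between-site variation in its error term (3 df when service terms are included).
- State that a heterogeneity test based on caller-level error will not be used to modify the model.
- Present the four service-level differences descriptively, labelled as intervention effect plus area difference. State that one site per arm per service does not allow the two to be separated.
- In the synthesis, use these differences to generate hypotheses only.

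This still allows differences between services to be examined. It needs changes of wording and no new data. The cost is that formal claims about the effect in a particular service are given up, which the design cannot support in any case.

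### Event rates are assigned to linear models, with no rule for when a count becomes a rate; for overdispersed rates this can lose power against a negative binomial model with a follow-up offset

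*Protocol article*

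**What the plan says.** Three statements in the protocol article bear on this.

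- Quantitative analysis assigns model families by type of variable: logistic for binary outcomes, then "negative binomial models for count variables and linear models for raw and transformed measurement outcomes, including rates".
- The same section says that numbers of events will be "converted to rates when appropriate". It does not say which outcomes this covers or what makes conversion appropriate.
- Data collection sizes the study on a rate: the 1200 expected callers are described as "allowing us to detect a change in rate of further emergency events/death of ±20% with 90% power and 95% confidence".

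Quantitative analysis also plans formal tests of whether outcomes are similar across services. The model may be modified afterwards, "for instance, allowing intervention outcomes to vary systematically from service to service". Covariate rules, missing data and reporting are left to a statistical analysis plan that is not shown. The model family for rates is not left to it; it is stated here.

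**The concern.** An event rate is a count divided by time at risk. Among people selected for frequent calling it will probably be right-skewed, with variance rising with the mean. Death is an outcome, so time at risk can be shorter than 6 months, and an unweighted linear model gives a rate from a few days the same weight as one from the whole period. The plan already has a suitable family, the negative binomial, but rates are sent elsewhere. The same events could be analysed in either branch depending on an undefined conversion.

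Two things are at stake. One is power for the case-management comparison. The other is how differences between services are read: a linear model on raw rates measures absolute differences, and these vary between services whenever a common rate ratio acts on different baselines.

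**Working it through.** **Inputs from the protocol.** 300 callers per service, 1200 in total; "four UK ambulance services with one intervention and one control site in each service"; follow-up of 6 months; ±20%, 90% power, 95% confidence. The Background gives 49 534 attendances by 1622 people in London, so 49 534/1622 = 30.5 per person-year, or about 2.5 a month. It gives no SD or dispersion.

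**Assumed.** 150 callers per site (600 per arm); two-sided 5% level; baseline rates of 1 to 5 events a month; dispersion k (variance = μ + kμ²) of 0.5, 1.1 or 2; 0 to 10% dying.

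**Step 1: the stated power.** (1.960 + 1.282)² = 10.51. With 600 per arm, 90% power for a relative 20% change needs one of these:

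- Negative binomial, mean 12 events (2 a month × 6), n per arm = 10.51 × (1/μ0 + 1/μ1 + 2k)/(ln RR)². For RR 0.8: 600 × 0.0498/10.51 = 2.84, so k = (2.84 − 1/12 − 1/9.6)/2 = 1.33. For RR 1.2: 600 × 0.0332/10.51 = 1.90, so k = (1.90 − 1/12 − 1/14.4)/2 = 0.87.
- Comparison of means: 600 = 2 × 10.51 × CV²/0.2², so CV = 1.07.
- Comparison of proportions: a control proportion of about 0.46.

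An absolute 20-point change from 50% would give over 99.9%. The 90% can be neither reproduced nor refuted. The central k of 1.1 below lies between the two values that a relative reading of a count would need.

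**Step 2: the scale.** With a common RR of 0.8 the absolute effect is −0.2 × baseline. Baselines of 1, 2, 3 and 4 a month give −0.2, −0.4, −0.6 and −0.8. The log rate ratio is ln 0.8 = −0.223 in every service. With equal baselines the absolute effects are equal too.

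**Step 3: simulation.** Negative binomial counts, RR 0.8 in all four services, service fixed effects. Three analyses: negative binomial with log follow-up offset (NB), linear on the raw rate, and linear on log(rate + 1/6). There were 300 replicates per setting (250 with prior use), so Monte Carlo error is about ±3 to 5 points. Entries are NB / raw / log, in %. The last column is the rejection rate at the 5% level when the true rate ratio is identical everywhere.

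| Baselines per month | k | Deaths | Prior use (log SD) | Power | Service-by-arm test |
|---|---|---|---|---|---|
| 2, 2, 2, 2 | 2 | 0 | none | 79 / 79 / 63 | 5 / 5 / 6 |
| 2, 2, 2, 2 | 2 | 10% | none | 77 / 77 / 59 | 5 / 5 / 5 |
| 1, 2, 3, 4 | 0.5 | 0 | none | 100 / 100 / 100 | 4 / 33 / 5 |
| 1, 2, 3, 4 | 1.1 | 0 | none | 94 / 92 / 86 | 6 / 18 / 3 |
| 1, 2, 3, 4 | 1.1 | 10% | none | 95 / 92 / 89 | 5 / 17 / 3 |
| 1, 2, 3, 4 | 2 | 0 | none | 73 / 66 / 54 | 6 / 11 / 8 |
| 1, 1.5, 2.5, 5 | 0.5 | 0 | none | 100 / 100 / 100 | 3 / 52 / 6 |
| 1, 1.5, 2.5, 5 | 1.1 | 0 | none | 94 / 84 / 81 | 7 / 31 / 2 |
| 1, 1.5, 2.5, 5 | 2 | 0 | none | 74 / 59 / 53 | 6 / 22 / 9 |
| 2, 2, 2, 2 | 1.1 | 5% | 0.7 | 92 / 80 / 84 | 2 / 4 / 4 |
| 1, 2, 3, 4 | 1.1 | 5% | 0.7 | 94 / 70 / 85 | 4 / 15 / 5 |

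With equal baselines, k = 1.1 and no covariate, NB and raw linear both had 94% power. The largest raw-scale loss was 93.6 − 70.4 = 23.2 points. After the log transform, with k of 1.1 or more, losses were mostly 6 to 20 points and at most 22 (79.3 − 57.3; baselines 1, 2, 3, 4, k = 2, 10% deaths). The share of deaths hardly changed the losses; unequal baselines and the skewed prior-use covariate drove those on the raw scale. With RR = 1 all three analyses stayed near 5% on both tests.

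**Step 4: how wide the baselines must be.** In a separate run with 6-month means of 6, 10, 14 and 20, k = 1, RR 0.8 and a prior-use log SD of 0.5, the service-by-arm test rejected in 17% (raw), 6% (logged) and 4.5% (NB). With means of 10, 12, 13 and 15 the raw figure was 5.2%, so no inflation.

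**The case against.** The strongest reply is that the plan already uses the recommended family where it matters. Calls, attendances and admissions over a common 6-month window are counts, counts go to negative binomial models, and conversion to rates is optional. The linear branch allows a transformation, and the unseen analysis plan may settle both. The simulated data were also multiplicative negative binomial, which favours that model, and the planned multilevel model was not fitted.

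Much of this stands, and it rules out four stronger readings that a reader might infer:

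- *That calls will be analysed by linear models.* The protocol permits this but does not say it.
- *That linear models on rates always lose power.* The raw-scale model lost none with equal baselines and no covariate.
- *That the planned modification of the model would be triggered falsely.* The assumption to be tested is that usual-care outcomes are similar across services, and likewise outcomes at intervention sites. It concerns outcome levels. With widely different baselines it is truly false, and modifying the model is right. Background information and descriptive summaries also feed that decision. What depends on scale is the narrower question of whether the effect differs by service, and the absolute differences are themselves real.
- *That the analysis is on a different scale from the power claim.* The protocol does not say whether ±20% is relative or absolute, and events/death could be a binary composite analysed by logistic regression.

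The reply does not remove the core. The family for rates is stated rather than deferred, the conversion has no criterion, and the permitted log transform cures the scale artefact but not the loss of power.

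**Conclusion.** The point holds in a conditional form. Event outcomes, and possibly the rate on which the study is sized, can fall into a linear branch that suits overdispersed rates less well than a negative binomial model with a follow-up offset.

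The direction is well supported. The size rests on assumed baselines, dispersion, prior-use spread and a multiplicative effect, none of which the protocol gives. Under those assumptions the raw-scale loss runs from nothing to about 23 points. Prior use is a planned adjustment, and with a skewed prior-use covariate at k = 1.1 the loss was 12 points (92% v 80%) even with equal baselines. The log transform leaves a loss of usually about 6 to 20 points where dispersion is 1.1 or more.

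Spurious service-by-arm differences (11 to 52% rejection against 2 to 7% for negative binomial) arise only on the raw scale, with widely unequal baselines and a non-null common rate ratio.

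**What to change.** In Quantitative analysis, delete the closing reference to rates from "negative binomial models for count variables and linear models for raw and transformed measurement outcomes, including rates". State that event rates are analysed as counts with a negative binomial mixed model, with log(days alive and in follow-up) as offset, and reported as adjusted rate ratios. Test service-by-arm differences on the rate-ratio scale. Keep linear models for true measurements such as costs. Converting counts to rates can then remain as a descriptive step.

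The cost is wording in the protocol and analysis plan; no new data are needed. Absolute differences, useful for the economic evaluation, can still be derived from the fitted model.
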